#### Sample Size

The required sample size was estimated using the G*Power program (Heinrich-Heine-Universität Düsseldorf) for repeated measures with 2 groups, 9 measured variables, power of 0.80, α set at .05, an estimated Cohen effect size of 0.25, and a correlation coefficient of 0.5. The sample size for each group was calculated as 36. By allowing for a potential 25% dropout rate, as suggested by Goyal et al [31], a final sample size of 96 participants (48 participants in each group) was established.

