**Methods:**

A 2 arms, double-blind, randomized controlled trial will be conducted over a 9-month period, with strategies designed to enhance treatment fidelity. The study expects to enroll 96 patients with T1D, aged 16 to 25 years. Participants will be randomly assigned to either the experimental or control group through central randomization. The intervention will be implemented using the Healthcare CEO app, which consists of 11 interfaces. The research will compare differences in disease control outcomes, confidence in self-management, self-care behaviors, emotional distress, quality of life, and specific diabetes-related knowledge between the 2 groups at baseline and 3, 6, and 9 months after intervention. Additionally, changes within the experimental group will be analyzed before and after the intervention.

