### Data Collection

Three research assistants with a background in health care, who have a basic understanding of T1D, have undergone training, and are not involved in the provision of health care, will be responsible for the data collection. Attending physicians of patients with T1D will provide referrals of patients who meet the inclusion criteria. One research assistant in charge of data collection will then approach the patients to explain the purposes of the study and the research process. Patients who agree to participate will subsequently fill out the informed consent sheet and undergo the preintervention test (T0) in an undisturbed environment. The second research assistant will obtain the randomization results from the statistician by phone and assist participants in downloading the Healthcare CEO app onto their smartphones based on their group assignment. The third research assistant will check and remind the second research assistant of the intervention steps to ensure the accuracy and completeness of the intervention. Considering that HbA_1c_, the critical indicator of blood glucose control, is measured once every 3 months, the time points for the postintervention data collection for both groups are set at 3 months (T1), 6 months (T2), and 9 months (T3) after the intervention.

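### The sample size calculation uses 9 measurements where the trial has 4 visits; on the plan's other inputs, 36 completers per group gives power of about 0.75, not 0.80

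*Protocol article*

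**What the plan says.** The Sample Size section of the protocol article gives a complete set of inputs. The software is named ("The required sample size was estimated using the G*Power program"), and the calculation is "for repeated measures with 2 groups, 9 measured variables, power of 0.80", with "α set at .05, an estimated Cohen effect size of 0.25" and a correlation of 0.5. The result is: "The sample size for each group was calculated as 36". A 25% dropout allowance then takes this to 48 per group and 96 in total.

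The measurement schedule is given twice. The Methods paragraph of the abstract has the groups compared "at baseline and 3, 6, and 9 months after intervention". The Data Collection section has a pre-intervention test (T0) and says that the later time points "are set at 3 months (T1), 6 months (T2), and 9 months (T3"). That makes four measurements of each outcome, and no section schedules nine.

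The Primary Outcomes section lists four variables: HbA1c, the percentage with HbA1c below 7.0%, and the numbers of hyperglycemic and hypoglycemic events. The Secondary Outcomes section lists five scales: self-management, self-care, distress, quality of life and knowledge.

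**The concern.** In a repeated-measures power calculation, the number of measurements is the number of times the same outcome is observed on the same person. Averaging those observations reduces noise, so a larger number lowers the required sample size. A knowledge or distress score does not make a participant's mean HbA1c more precise. If the number of outcome variables was entered in that place, the calculation credits the trial with precision that four visits cannot supply.

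The figures at stake are the 36 per group and the power of 0.80, which readers will use to judge the final result. If they do not follow from the design as described, they need restating before results are reported. Recruitment is described as ongoing, so there is time.

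**Working it through.** **Inputs, all from the Sample Size section unless noted.** Effect size f = 0.25 (read as Cohen's f, since this is a G\*Power F test), k = 2 groups, correlation ρ = 0.5, α = 0.05, target power 0.80, stated number m = 9, dropout 25%. Scheduled number of measurements m = 4 (abstract and Data Collection).

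**Formula.** For the between-factors repeated-measures test, the noncentrality parameter is λ = f²·N·m / (1 + (m − 1)ρ), with k − 1 = 1 and N − 2 degrees of freedom. Power comes from the noncentral F distribution.

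**Step 1: reproduce the stated figure (m = 9).**
- N = 70: λ = 0.0625 × 70 × 9 / 5 = 7.875, power 0.790.
- N = 72: λ = 0.0625 × 72 × 9 / 5 = 8.1, power 0.8015.

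The smallest even N is 72, or 36 per group. Then 36 / 0.75 = 48 per group and 96 in total. Both stated figures are reproduced exactly.

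**Step 2: check whether another route gives 72.**
- The group-by-time interaction test with the default effect size needs N = 16 (m = 9) or 24 (m = 4).
- The same test with the SPSS-style effect size needs 34 (m = 9) or 62 (m = 4).
- Within the between-factors test, m = 8 needs 74. Values of 10 and 11 also give 72, but 9 is the number in the text.

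Of the variants tried, only the between-factors test gives 72.

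**Step 3: replace 9 with the scheduled number, all else unchanged.**

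| Measurements | N | λ | Power |
|---|---|---|---|
| 4 (T0–T3) | 72 | 0.0625 × 72 × 4 / 2.5 = 7.2 | 0.754 |
| 4 (T0–T3) | 82 | 0.0625 × 82 × 4 / 2.5 = 8.2 | 0.808 |
| 4 (T0–T3) | 96 | 0.0625 × 96 × 4 / 2.5 = 9.6 | 0.866 |
| 3 (T1–T3) | 72 | 0.0625 × 72 × 3 / 2 = 6.75 | 0.727 |
| 3 (T1–T3) | 86 | 0.0625 × 86 × 3 / 2 = 8.06 | 0.801 |

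With m = 4, N = 80 gives 0.798, so 82 (41 per group) is the smallest even N that reaches 0.80. After dropout, 41 / 0.75 = 54.7, which rounds up to 55 per group, or 110 in total.

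**Step 4: an alternative contrast for the same 36 per group.** With two groups, f = 0.25 corresponds to a standardised difference d = 0.5. Assume that this difference holds at each post-baseline visit and that ρ = 0.5 between all visits.
- Variance of the mean of T1–T3: (1 + 2 × 0.5) / 3 = 0.667.
- After adjustment for T0: 0.667 − 0.5² = 0.417.
- Standard error of the difference: √(0.417 × 2 / 36) = 0.152.
- Ratio: 0.5 / 0.152 = 3.29. Power is about 0.90.

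**The case against.** **The mechanism is inferred.** The section does not name the G\*Power test, the field that received the 9, or what the nine variables are. This stands in part. The count of 4 + 5 outcomes fits, but the aims in the Knowledge Gaps and Conceptual Framework sections omit knowledge, which would give eight. The origin of the 9 is therefore only probable. The finding does not depend on it: 9 is not the number of visits, and the stated 36 is reproduced with 9.

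**The shortfall is modest.** This stands. It is 4.6 percentage points of power, or five participants per group before dropout. If all 96 were retained, power at four visits would be 0.866, and the Statistical Analysis section keeps participants with missing values in the model. A correlation of 0.4 instead of 0.5 would bring power at N = 72 back to 0.805. Still, the plan itself assumes 25% dropout and a correlation of 0.5, and 0.80 does not follow on those terms.

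**The planned analysis is GEE, and an unseen analysis plan may say more.** Neither repairs a fully stated calculation whose input conflicts with the visit schedule. But this objection limits what can be concluded. A reader might infer that the trial is underpowered. The documents do not support that: at 36 per group the baseline-adjusted mean of T1–T3 has power of about 0.90, and an interaction test with f = 0.25 at four visits has 0.87 or more at N = 72. A reader might also compute lower power for the 9-month visit alone, or for an average diluted by T0. The Sample Size section names neither as its target, so such figures would not measure this error. Nor can the shortfall be put in HbA1c units: the only standard deviation given (1.9%, in the Introduction) comes from a US registry, not from patients selected on HbA1c as here.

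**Conclusion.** The calculation is wrong as written. The stated 36 per group matches a between-factors test with nine measurements, while the trial schedules four. On the plan's own remaining inputs, 36 completers per group gives power of about 0.75 instead of 0.80, or 0.73 if only the three post-baseline visits count. Reaching 0.80 with four visits would take 82 completers, or 110 enrolled.

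This rests on three readings: 0.25 is Cohen's f, the between-factors test was used (the only variant tried that returns 36), and the correlation is 0.5 between all visits. The conclusion is confined to the stated sample-size figure and says nothing general about the power of the GEE contrasts.

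**What to change.** Keep the enrolment target of 96 and correct the Sample Size paragraph. Replace the 9 with the actual number of visits and name the G\*Power test used. Restate the power as about 0.75 at 36 completers per group and 0.87 if all 96 are retained, and name the contrast to which it applies.

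Alternatively, base the statement on a baseline-adjusted mean of T1–T3, with power of about 0.90 at 36 per group under d = 0.5 and correlation 0.5. This option requires that contrast to be the one actually tested.

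Either way the cost is one rewritten paragraph and no extra participants. Under the first option the stated power becomes less favourable.

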### Data Analysis

#### Statistical Analysis

The intention-to-treat principle will be used for the data analysis; that is, all participants will be included in their initially assigned groups for analysis, regardless of whether they withdraw from the study for any reason or are lost to follow-up. Data will be analyzed using IBM SPSS 26.0 for Windows, with differences considered statistically significant at *P*<.05. Demographic and disease status data, including age, gender, BMI, age at diagnosis, disease duration, and HbA_1c_, along with metrics on the app usage to evaluate treatment fidelity, such as the log-ins to the app, frequency of use for each interface, number of e-books read in the CEO Knowledge Base, and number of online consultations in CEO’s Secretary, will be presented through descriptive statistics. This will include frequency distributions, percentages, means, SDs, and maximum and minimum scores. Homogeneity in the essential attributes of the 2 groups will be compared and analyzed using inferential statistics, such as the chi-square test and ANOVA. Owing to the longitudinal nature of this study, repeated data measurements will be taken. Dependencies may exist among the data at different time points, and data loss may also occur. Using generalized estimating equation models, repeated measurements can be simultaneously included in the regression analysis. Through the variance correction process, consistent estimates of the regression parameters and their variance can be provided to correct for dependencies, and participants with missing values can still be included in the analysis [52]. Therefore, a generalized estimating equation will be used for data analysis to compare the differences between the experimental and control groups at both preintervention and postintervention time points, as well as the differences in the scores of the experimental group before and after intervention.

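### The stated 0.80 power fits a group difference averaged over 9 measurements; the visit-wise comparison the protocol describes has about 0.55 to 0.68 on the same inputs

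*Protocol article*

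**What the plan says.** The Sample Size section describes a G*Power calculation "for repeated measures with 2 groups, 9 measured variables", with "power of 0.80, α set at .05, an estimated Cohen effect size of 0.25, and a correlation coefficient of 0.5". It gives the result as "The sample size for each group was calculated as 36", and a 25% dropout allowance takes this to 48 per group, 96 in all. It does not say which repeated-measures test was chosen.

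The Statistical Analysis section plans a generalized estimating equation (GEE) to "compare the differences between the experimental and control groups at both preintervention and postintervention time points", together with a before-and-after comparison inside the experimental group. The abstract says the outcomes will be compared "between the 2 groups at baseline and 3, 6, and 9 months after intervention". The Data Collection section schedules four occasions: T0, and T1, T2 and T3 at 3, 6 and 9 months. No section states a group effect averaged over visits.

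**The concern.** Averaging several correlated measurements reduces the variance of the group comparison. A power figure that relies on this averaging does not carry over to a comparison at one visit. If 0.80 belongs to the averaged test while the results are presented visit by visit, readers will credit each visit result with more power than it has. A non-significant difference at 3, 6 or 9 months could then be taken as sound evidence against the app. The protocol's own introduction calls the earlier evidence on such apps inconsistent, so that misreading would matter.

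**Working it through.** **Inputs.** All are from the Sample Size section: f = 0.25, correlation ρ = 0.5, α = 0.05, m = 9 measurements, N = 72 (36 per group) before dropout. For two equal groups, d = 2f = 0.5. The outcome SD is set to 1.

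**Step 1: reproduce the printed size.** The between-factors test has noncentrality λ = N f² m / (1 + (m − 1)ρ), with 1 and N − 2 degrees of freedom.
- N = 72: λ = 72 × 0.0625 × 9 / 5 = 8.1, power 0.8015.
- N = 70: λ = 7.875, power 0.790.

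So 72 is the smallest even total that reaches 0.80, and it matches the printed 36 per group. The dropout step also reproduces: 36 / (1 − 0.25) = 48.

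**Step 2: try the alternatives.** The within-between interaction with λ = N f² m / (1 − ρ) needs a total of 16 for m = 9, or 24 for m = 4. With λ = N f² it needs 242 or 176. Between factors with m = 4 needs 82. None of these gives 72.

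**Step 3: power of the visit-wise comparison.** This is a two-sided two-sample t test with standardised effect δ = 0.5/√v and noncentrality δ√(n/2), where v depends on the analysis:
- Unadjusted difference at one visit: v = 1.
- Change from T0 to one visit: v = 2(1 − ρ) = 1, so the power is the same.
- One visit adjusted for T0: v = 1 − ρ² = 0.75, δ = 0.577.

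| Comparison at one visit | 36 per arm | 48 per arm (no dropout) |
|---|---|---|
| Unadjusted, or change from T0 | 0.553 | 0.679 |
| Adjusted for T0 | 0.676 | 0.799 |

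A joint 3-df group-by-time test with d = 0.5 at T1, T2 and T3 has noncentrality 6.75 and power of about 0.56 at 36 per arm.

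**Step 4: power of averaged contrasts at 36 per arm.**
- Average of T0 to T3 with no difference at T0, as randomisation implies: effect 0.5 × 3/4 = 0.375, variance (1 + 3 × 0.5)/4 = 0.625, power 0.510.
- Average of T1 to T3, unadjusted: variance (1 + 2 × 0.5)/3 = 0.667, power 0.727.
- Average of T1 to T3, adjusted for T0: variance 0.667 − 0.25 = 0.417, power 0.900.

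Part of the gain from 0.55 to 0.90 therefore comes from averaging (to 0.73) and the rest from baseline adjustment.

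**Step 5: the measurement count.** Nine measurements do not match the four scheduled occasions. With m = 4 the averaged test has λ = 72 × 0.0625 × 4 / 2.5 = 7.2 and power 0.754. That is a separate issue: correcting it still yields a figure for the averaged test, not for a visit.

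**The case against.** The strongest reply is that one inferred test is being set against another. The sized routine is identified only by reproduction. The Statistical Analysis section does not spell out the GEE contrast, and a protocol article may leave that to an analysis plan. This stands in part. A reader might infer that the planned analysis never tests an average, but the text supports only that no averaged effect is stated. It does not exclude one.

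A second reply is that 0.55 is near the low end. Baseline adjustment raises it to 0.68. The GEE also keeps participants with incomplete data, so early visits may have more than 36 per arm. A higher correlation helps too: at ρ = 0.7 and 36 per arm, a change score has 0.77 and a baseline-adjusted visit 0.83. This also stands, and is why the power is given as a range. However, the protocol states ρ = 0.5, allows for 25% dropout and mentions no baseline adjustment.

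Third, one might infer that the whole trial has only an even chance of showing an effect. That goes too far. If d = 0.5 holds at all three follow-up visits, simulation puts the chance that at least one unadjusted visit test is significant at about 0.80. That figure carries no multiplicity control, so it does not rescue the stated power, but it shows that 0.55 describes a single visit.

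Finally, reading 0.25 as an interaction effect would give power above 0.99 at N = 72 with four occasions. That reading does not return 36 per group.

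**Conclusion.** The point holds in a limited form. The printed 36 and 48 are not arithmetic errors, because both reproduce. The difficulty is that the 0.80 attached to them fits a comparison the document does not describe. For the comparison it does describe, power at one visit is about 0.55 unadjusted or as change from baseline, and about 0.68 with baseline adjustment, at 36 evaluable per arm. With all 48 per arm retained, the figures are about 0.68 and 0.80. None of these readings restores 0.80 under the protocol's own correlation and dropout allowance.

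This rests on four assumptions: the sized routine is as inferred, f = 0.25 means d = 0.5 at the visit in question, ρ = 0.5, and testing is two-sided at 5%.

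**What to change.** Either of two changes would do.

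1. In the Sample Size section, name the G*Power test used and restate the power for the visit-wise comparison as about 0.55 (unadjusted) to 0.68 (baseline-adjusted) at 36 per arm. The cost is a less favourable stated figure.

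2. In the Statistical Analysis section, prespecify as the primary contrast the group difference averaged over T1, T2 and T3, adjusted for T0, with visit-wise differences as supportive. On the stated inputs this has about 0.90 power at 36 per arm, of which averaging alone gives about 0.73. It needs no more participants. The cost is that the estimand describes the effect over the 9 months rather than at month 9.

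Whichever is chosen, correct the measurement count alongside it, since 9 does not match the four occasions.

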#### Sample Accessibility

The cumulative number of patients in the transition phase, aged 16-25 years, at the study site is expected to exceed 300. For each enrolled participant, the study explanation and data collection process is expected to last approximately 1 hour. Based on our research team’s qualitative research experience, the on-site interview length for each participant was 1-1.5 hour, whereas the refusal rate is expected to be approximately 10%. Therefore, each week, approximately 8 patients who fulfill the inclusion criteria will participate in the study. Thus, the number of valid samples expected each month is roughly 28-32.

### Randomization and Blinding

Randomization of the participants will be performed by a statistician, using the central randomization method in SPSS (IBM Corp). During participant enrollment, participants will be randomly assigned to the experimental or control groups in accordance with the instructions provided on the phone by the statistician; the participants and data collectors will be blinded to allocation. Blinding strategies include the following. First, the statistician will not be allowed to disclose the randomization results to others. Second, once a physician referral is received, the participant will be promptly taken to a private room. The data collection assistant will complete their duties and leave the room, and then 2 research assistants will come in and take over to administer the intervention phase. Third, participants of both the experimental and control groups will download the app, but the app content will differ. Fourth, to avoid differential demand characteristics, research assistants will emphasize to all participants that app usage is potentially beneficial for disease management.

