## Methods

### Design

A 9-month, 2-arm, parallel-group, double-blind, randomized controlled trial will be conducted. Participants will be randomly assigned to the experimental or control groups, and treatment fidelity monitoring strategies will be adopted to enhance the consistency and fidelity of intervention measures.

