CEO’s Secretary	This consists of 2 functions, namely “Reminders” and “Online consultations.” (1) Reminders: When trends of exceedances related to blood glucose occur, such as excessively high postdinner blood glucose level for 3 consecutive days, noninput of health data for ≥3 days, fewer blood glucose measurements than the required number of measurements for 3 days, and on the day before a scheduled outpatient visit, patients and app administrators will receive notifications and text message reminding them to perform relevant tracking actions. Reminders can also be set based on the needs of the patients; (2) Online consultations: The timing and theme of online consultation sessions can be booked in advance. Online consultations involve the clarification of doubts related to disease care through interactions with health care professionals.	Assist in disease management and provide individualized knowledge to enhance disease-related knowledge and confidence in self-care, thereby alleviating emotional distress and improving disease-related QoL Conditions for reminders can be set to reduce annoying reminders, to prevent resentment of app use
Who’s the Best CEO	One point is awarded every time the user performs data input on time, reads an article, devises a communication technique, and correctly enters data into the Help Me, Detective! interface, or enquires about online consultation. Ten points are awarded when the target HbA_1c_ level is reached. The patients with the highest number of points are listed weekly. At the end of each month in our study, the top 3 patients with the highest number of points will each receive an NT $300 (approximately US $9.24) voucher. Moreover, at the end of the study, the top 3 patients with the highest number of points will receive an NT $1000 (approximately US $30.79) voucher.	Enhance motivation and effort in self-care
SOS calls	Patients can set up 3 contact numbers to call for help quickly when necessary.	Assist in disease management and self-care, thereby improving disease control outcomes
Q&A	Patients who may be unaccustomed to asking questions in the chat room can have their queries answered via the provided email account.	Assist in disease management and self-care to improve outcomes

^a^HbA_1c_: hemoglobin A_1c_.

^b^T1D: type 1 diabetes.

^c^QoL: quality of life.

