#### Experimental App Intervention

The complete Healthcare CEO app will be used to intervene in the experimental group. Two trained research assistants will supervise each other to guide the participants in the following aspects, according to the standard treatment manual: (1) account setup; (2) viewing of operation guidance videos; (3) demonstration of all app functions, getting participants to perform app operations, and clarifying doubts about app usage; (4) explaining troubleshooting methods; (5) providing contact information of app administrators; and (6) setting a HbA_1c_ control target. Between every 2 rounds of data collection, the research assistants will contact the participants to check if they have encountered issues or difficulties when using the app, although they will not exchange disease care-related information. After the completion of data collection, the app will be remotely uninstalled by the administrators at the backend.

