#### Control App Intervention

Participants in the control group will only install the “CEO’s Profile” and “Health Tracking” interfaces of the Healthcare CEO app. In addition to explanations for the account setup and the use of the 2 interfaces, the research assistants will not provide any app-related information to the control participants. The status and difficulties of app use will also not be tracked. After the last round of data collection, the full version of the Healthcare CEO app will be provided to the control group participants, according to their preferences. The app will be remotely uninstalled at the backend by the administrators after 9 months.

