### Ethical Considerations

The study will follow the Declaration of Helsinki and has received approval from the Ethics Committee of the Chang Gung Foundation Institutional Review Board (submission reference: 202100050B0; March 9, 2021). It will uphold key ethical principles, including informed consent, with participants receiving comprehensive information about the study. For minors, consent will be obtained from a legal guardian simultaneously, and efforts will be made to minimize any undue influence from guardians or family members to guarantee voluntary participation. Participants may withdraw at any time without impacting their medical care. The study prioritizes participant safety through self-reported questionnaires and a mobile app that poses no risks. Justice is maintained by ensuring equal medical care for all participants, with the control group accessing the app after the study. Privacy is protected with data secured in locked storage and coded identifiers used in publications to ensure anonymity. Participants will receive a voucher worth NT $300 (approximately US $9.34) for each completed questionnaire as an appreciation for their time and effort.

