## Discussion

### Principal Findings

The Healthcare CEO app distinguishes itself as one of the few evidence-based, multifunctional integrated apps specifically designed for individuals aged 16-25 years managing T1D. This study uses a double-blind, randomized controlled trial intervention, with anticipated outcomes aimed at enhancing disease knowledge, improving self-care skills, and strengthening self-efficacy in disease management. Additionally, training in effective communication skills is intended to reduce interpersonal and emotional distress, enhance QoL, and ultimately improve glycemic control outcomes. The strengths and limitations of this study are elaborated in the following sections.

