### Limitations

This study design has several limitations. First, the app usage may be limited by an unstable internet connection, which could impact the effectiveness of our app-based intervention. Second, in addition to providing gift vouchers to enhance the motivation and efforts of the participants, we also factored in an allowance during sample size estimation to minimize the effects of participant withdrawals. Third, because of the nature of the study, the researchers cannot be blinded during the study implementation, which may lead to potential biases. To address this issue, researchers must adhere to strict intervention principles to minimize the impact on the study results. Finally, the Healthcare CEO app was developed and will be evaluated based on Taiwanese participants with T1D in the transition phase. Therefore, caution will have to be exercised, and cultural differences will be considered when interpreting the study results.

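### The trial is labelled double-blind, but the described measures do not secure participant blinding, so blinding cannot be claimed for the four participant-reported scales

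*Protocol article*

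**What the plan says.** The double-blind label appears in the Abstract (Methods), in Methods, Design ("A 9-month, 2-arm, parallel-group, double-blind, randomized controlled trial will be conducted") and in Discussion, Principal Findings ("This study uses a double-blind, randomized controlled trial intervention"). Randomization and Blinding specifies who is meant: "the participants and data collectors will be blinded to allocation". Of the four measures listed there, two bear on what a participant perceives after allocation. Both arms download an app, although with different content, and all participants hear the same statement that using it may be of benefit.

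Under Experimental App Intervention, participants get the complete app. Their session includes "demonstration of all app functions, getting participants to perform app operations", and staff contact them between data-collection rounds about difficulties with the app. Table 1 describes what the app contains, including chat rooms, bookable online consultations and a points scheme: "The patients with the highest number of points are listed weekly". Under Control App Intervention, participants get only the profile and health-tracking interfaces, and their use and difficulties are not followed up.

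The Limitations section addresses blinding once: "because of the nature of the study, the researchers cannot be blinded during the study implementation". It does not mention participants.

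**The concern.** Four secondary outcomes are participants' own ratings, completed online: the Perceived Diabetes Self-Management Scale, the Self-Care Behavior Assessment Scale, the Diabetes Distress Scale and Diabetes Quality of Life. For these scales, blinding the data collector gives little protection, because the participant is the assessor. Someone who recognises that they hold a rich or a sparse version of the app may answer accordingly, and a between-group difference could then appear without any effect of the app. Table 1 names confidence, self-care, distress and quality of life among the things the additional interfaces are meant to improve, so expectation and hypothesis point the same way. A reader who sees the double-blind label will take differences on these scales as protected from that bias.

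**Working it through.** **1. What each arm sees, side by side**

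| Feature | Experimental | Control |
|---|---|---|
| Interfaces | 11 | 2 (so 11 − 2 = 9 are absent) |
| Chat rooms, two themed chats a month | yes | no |
| Weekly ranking; monthly and end-of-study ranking vouchers | yes | no |
| Bookable consultations with professionals | yes | no |
| Staff contact about app use between rounds | yes | no |
| Message that app use may help | yes | yes |
| Setting an HbA1c target in Health Tracking | yes, guided by staff | available in the interface |
| NT $300 voucher per completed questionnaire | yes | yes |

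The last three rows are wholly or largely common to both arms and say little about unmasking. The first five differ openly and last throughout follow-up. Neither participant-level measure conceals them: sharing a download leaves the content different, and sharing a message leaves the experience different. Under Data Collection, T0 is completed before the allocation is obtained, so the exposure concerns T1, T2 and T3.

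**2. The plan's own sample size**

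Inputs from Sample Size: f = 0.25, correlation ρ = 0.5, m = 9 measurements, α = .05, power 0.80. With the between-groups repeated-measures formula, λ = f²·N·m / [1 + (m − 1)ρ]. At N = 72, λ = 0.0625 × 72 × 9 / 5 = 8.1, which gives power 0.801, that is, 36 per group. Allowing for dropout, 36 / (1 − 0.25) = 48 per group, 96 in total. Both stated figures reproduce, and 36 and 48 per arm are used below. Whether m = 9 is the right input is a separate matter.

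**3. Illustration of what a reporting shift could do**

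The documents give no size for such a shift, so 0.1, 0.2 and 0.3 SD are assumed, with no true effect. For one scale at one visit, use a two-sample t test at two-sided 5%, with noncentrality δ = d·√(n/2).

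- n = 36: √18 = 4.243, so δ = 0.42, 0.85, 1.27. The chance of P<.05 is 0.070, 0.133, 0.241.
- n = 48: √24 = 4.899, so δ = 0.49, 0.98, 1.47. The chance of P<.05 is 0.077, 0.163, 0.307.

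With no shift the figure is 0.050.

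The plan analyses repeated measures by generalized estimating equations, so a single-visit t test is a simplification. Averaging over the three post-baseline visits with ρ = 0.5 and 36 per arm, the formula in step 2 with f = d/2 and m = 3 gives 0.081, 0.176, 0.337. Averaging over visits does not remove a constant shift; it makes the shift easier to detect.

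**The case against.** The strongest reply is that arms which can be told apart are not the same as allocation being known. Each participant sees one version, and the two-interface app could pass for a complete product. A reader might infer that the trial is in effect open-label. The documents do not support that, because the consent material is not shown. The article's statement on consent, "with participants receiving comprehensive information about the study", does not say that the content of the other arm is disclosed. Some controls may remain unsure which arm they are in. This objection stands, and it limits the point to blinding that is not secured, rather than blinding shown to have failed.

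Some apparent evidence of unmasking is also weak. The article says that "the full version of the Healthcare CEO app will be provided to the control group participants", but only after the last round of data collection, so this could influence answers only if controls were told in advance, which the article does not say. Target-setting and the questionnaire voucher are not exclusive to one arm.

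It is also fair that the article says openly that content differs, that the common message is aimed at differential demand, and that these scales are already secondary. The message does reduce differential expectation. None of this supports an unqualified statement that participants are blinded.

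On size, the shift is an assumption. A larger headline could be had by asking for significance on at least one of the four scales, but that would mix in multiplicity, a different issue, so it is not used here.

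Finally, a reader might conclude that effectiveness should be judged on venous HbA1c alone. That does not follow. Primary Outcomes lists four measures, including hyperglycemic and hypoglycemic events, and nothing here argues for changing that set.

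**Conclusion.** The point holds for participants and for the four self-report scales. The article claims participant blinding, describes arms that differ visibly for nine months, offers no measure that hides the difference, and limits its stated limitation to researchers. Blinding therefore cannot be claimed for confidence, self-care, distress and quality of life. The article does not establish whether any given participant knows the allocation.

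The size is illustrative. At 36 per arm, assumed shifts of 0.1 to 0.3 SD raise the false-positive chance on one scale at one visit from 5% to between about 7% and 24%. This rests on the assumed shift being the average across the arm, a two-sided test and no true effect.

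Laboratory HbA1c is not open to this reporting bias. The knowledge questionnaire is scored on correct answers, so the argument is weaker there and it is not counted among the four scales.

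**What to change.** - **Abstract; Methods, Design; Discussion, Principal Findings:** replace the double-blind label with a description of who is masked.
- **Randomization and Blinding:** withdraw the statement that participants are blinded. Say that they receive visibly different versions of the app, so their blinding cannot be assured. The common message can stay, described as a measure to reduce differential expectation.
- **Limitations:** extend the blinding limitation from researchers to participants and name the four self-report scales.
- **Reporting:** state that between-group differences on these secondary scales are supportive and open to expectancy bias. Leave the primary outcome set unchanged, and note that laboratory HbA1c is not open to this reporting bias.

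The cost is a less favourable design label and a weaker claim from the self-report scales. No new data, staff or participants are needed. The article describes the findings as still to be finalised, so the wording can be corrected before the final report.
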